# Study protocol of a randomized phase III trial of comparing preoperative chemoradiation with preoperative chemotherapy in patients with locally advanced gastric cancer or esophagogastric junction adenocarcinoma: PREACT

**DOI:** 10.1186/s12885-019-5728-8

**Published:** 2019-06-20

**Keywords:** Gastric cancer, Esophagogastric junction adenocarcinoma, Preoperative chemotherapy, Preoperative Chemoradiation, Gastrectomy, Adjuvant chemotherapy

## Abstract

**Background:**

The prognosis of patients with locally advanced gastric cancer or esophagogastric junction adenocarcinoma is still dismal. There are no standard treatment strategies for these patients. Multidisciplinary team (MDT) approach is a good choice for making a high-quality decision. Generally, MDT will recommend these patients to receive preoperative chemotherapy or preoperative chemoradiation based on all kinds of treatment guidelines. However, the preferred preoperative treatment is still not established. In order to solve this problem, we carry out this randomized phase III trial of comparing preoperative chemoradiation with preoperative chemotherapy in patients with locally advanced gastric cancer or esophagogastric junction adenocarcinoma.

**Methods:**

Eligible patients with locally advanced gastric cancer or esophagogastric junction adenocarcinoma are randomized to receive preoperative chemoradiation or preoperative chemotherapy, followed by surgery and postoperative chemotherapy. In the preoperative chemoradiation arm (Pre-CRT), patients receive two cycles of S-1 and oxaliplatin (SOX), chemoradiation, then followed by surgery and three more cycles of SOX chemotherapy. In the preoperative chemotherapy arm (Pre-CT), patients receive three cycles of SOX, following surgery three more cycles of SOX are given. The primary endpoint of this trial is to verify that preoperative chemoradiation could significantly improve the 3-year disease free survival (DFS) of patients with locally advanced gastric cancer or esophagogastric junction adenocarcinoma compared to preoperative chemotherapy.

**Discussion:**

The results from this trial will provide important information about whether preoperative chemoradiation could improve survival compared to preoperative chemotherapy among patients with locally advanced gastric cancer or esophagogastric junction adenocarcinoma.

**Trial registration:**

ClinicalTrials.gov Identifier: NCT03013010. First posted January 6, 2017.

## Background

Gastric cancer is still the sixth most common cancer around the world, and approximately 40% of new patients with gastric cancer are diagnosed in China [1]. Surgery is still the most effective treatment modality. However, most Chinese patients with gastric cancer lose the chance to undergo surgery due to being diagnosed as advanced stage. Among these patients, those with locally advanced stage still have potential opportunity to receive surgery after preoperative chemotherapy or chemoradiation, which is also recommended by the NCCN guideline [2]. Based on MAGIC and FNCLCC/FFCD trial, perioperative chemotherapy has been established as an alternative option for patients with resectable gastric cancer [3, 4]. Additionally, there are some preoperative chemoradiation reports in gastric cancer. A prospective, randomized trial showed that preoperative chemoradiation followed by surgery was superior to surgery in patients with resectable adenocarcinoma of the esophagus and gastric cardia [5]. Some phase II studies also showed that preoperative chemoradiation resulted in substantial pathologic response and R0 resection rate [6–8]. In our previous published research, 67% patients with locally advanced gastric cancer received curative gastrectomy after receiving chemoradiation [8]. Based on the publication of above-mentioned studies, clinicians have been faced with the dilemma of which preoperative therapy, chemotherapy or chemoradiation, should be applied to patients with locally advanced gastric cancer. A phase III study of comparing preoperative chemotherapy with chemoradiation was carried to solve this problem [9]. Unfortunately, this study was closed prematurely due to low accrual. Therefore, a randomized phase III trial comparing preoperative chemotherapy with chemoradiation is needed is deeply needed.

The aim of this study is to compare perioperative S-1 and oxaliplatin (SOX) chemotherapy with preoperative chemoradiation plus perioperative SOX chemotherapy in patients with locally advanced gastric cancer. Among the various chemotherapy regimes, S-1 and oxaliplatin (SOX) appears to be effective. Some studies have shown that SOX had a favorable tumor response rate with a relatively mild toxicity profile [10, 11].The study protocol of this trial, which has the acronym PREACT, is described in this article. This trial is an prospective, multicenter study be conducted in China.

## Methods/design

### Study setting

PREACT is a randomized phase III trial, which is carried out at multicenter in China. Eligible patients with locally advanced gastric cancer or esophagogastric junction adenocarcinoma are randomized to receive preoperative chemoradiation or preoperative chemotherapy, followed by surgery and postoperative chemotherapy (Fig. 1). Patients were randomized by the way of stratified permutated block randomization on Web-based system. Lauren classification is stratification factor. In Pre-CRT arm, patients receive two cycles of SOX plus chemoradiation, followed by surgery and three more cycles of SOX chemotherapy. In the Pre-CT arm, patients receive three cycles of SOX, following surgery three more cycles of SOX are given. The protocol has been approved by the Ethics Committee of Fudan University Shanghai Cancer Center, as well as other institutional ethics committees. All patients provided written informed consent before enrollment. Monitoring will be carried out in this trial.

**Fig. 1 Fig1:**
[figure not shown]
Flow chart

### Primary endpoint

3-year disease free survival (DFS).

### Secondary endpoint

3-year overall survival (OS), curative gastrectomy rate, pathological response rate, treatment toxicity, and postoperative complications.

### Recruitment

Patients with locally advanced, histologically confirmed gastric cancer or esophagogastric junction adenocarcinoma are recruited. All the patients should take following examinations: chest radiography, CT scan, and endoscopic ultrasonography. Six hundred and eighty-two patients will be enrolled in China. If the patients meets all the inclusion criteria, staging laparoscopy or laparotomy will be performed to exclude peritoneal dissemination.

### Inclusion criteria

Age ≥ 18 years.Eastern Cooperative Oncology Group performance status 0–1.Life expectancy ≥6 months.Histologically proven adenocarcinoma of the stomach or esophagogastric junction(excluding Siewert I).Clinical stage is stage IIB (T3 N1 only), IIIA (T2 N3 not eligible), IIIB, and IIIC, i.e. T3 -T4a and node positive, or T4b and/ or node positive, according to American Joint Committee on Cancer (AJCC) 7th edition.Considered to be potentially resectable verified by a multi-disciplinary team including a surgical investigator.Patients have adequate organ function as follows:
Haemoglobin ≥90 g/L, Absolute neutrophil count (ANC) ≥1.5 × 10^9^ /L, Platelet count≥100 × 10^9^ /LSerum bilirubin ≤1.5 × upper limit of normal, Aspartate aminotransferase (AST) and/or alanine transaminase (ALT) ≤2.5 × upper limit of normalSerum creatinine≤1.0 × upper limit of normal
8)Patients must provide the written informed consent.

### Exclusion criteria

Pregnant or lactating females or planning to become pregnant or lactating.There is evidence of metastatic disease.Prior chemotherapy or radiotherapy.Patients have a history of cancer in the five years before randomization except for the squamous or basal cell carcinoma of the skin that has been effectively treated, and carcinoma in situ of the cervix that has been treated by operation.Patients with central nervous system (CNS) disorder or peripheral nervous system disorder or psychiatric disease.Patients with known history of uncontrolled or symptomatic angina, uncontrolled arrhythmias and hypertension, or congestive heart failure, or cardiac infarction within 6 months prior to study enrollment, or cardiac insufficiency.Patients with severe infection.Patients with severe gastrointestinal bleeding, gastrointestinal perforation, or unable to swallow.Patients with known hypersensitivity reaction or metabolic disorder to S-1or oxaliplatin in this study.Patients with linitis plastica.

### Treatments

#### Chemotherapy

SOX consists of S-1 and oxaliplatin. A course of chemotherapy will last 21 days. S-1 is administered orally with 40–60 mg, twice a day for 14 consecutive days, followed by a 7-day rest period (Fig. 2). The dose of S-1 was accorded to body-surface area (BSA): patients with a BSA of less than 1.25 m^2^ receive 80 mg daily; those with a BSA of 1.25 m^2^ or more but less than 1.5 m^2^ receive 100 mg daily; and those with a BSA of 1.5 m^2^ or more receive 120 mg daily. Oxaliplatin 130 mg/m^2^, intravenously, on day 1.

**Fig. 2 Fig2:**
[figure not shown]
Chemotherapy schedule

#### Chemoradiation

Radiation is administered one week after completing the first cycle of chemotherapy. The treatment regimen consisted of 45 Gy of radiation delivered in 25 fractions ever five days per week for five weeks. Concurrent chemotherapy is S-1 40–60 mg/m^2^orally, oral tablet twice daily, days 1–5 of each week of radiotherapy (Fig. 3).Radiation treatment planning is done using computed tomography (CT) images. The radiation field includes the primary lesion and regional lymph node drainage.

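### Concurrent S-1 in the chemoradiation arm is printed per m², but the same figures are flat mg doses in the SOX section; the per-m² unit is probably a misprint

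*Protocol article*

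**What the plan says.** The Protocol article states the S-1 dose in two places under Treatments.

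- **Chemotherapy (SOX, both arms):** "S-1 is administered orally with 40–60 mg, twice a day for 14 consecutive days". The section then ties the amount to BSA in three bands. The lowest is worded "patients with a BSA of less than 1.25 m^2^ receive 80 mg daily". The middle band, from 1.25 to below 1.5 m², is set at 100 mg a day. The highest is worded "those with a BSA of 1.5 m^2^ or more receive 120 mg daily".
- **Chemoradiation (Pre-CRT arm only):** the drug given with radiation is stated as "S-1 40–60 mg/m^2^orally, oral tablet twice daily, days 1–5 of each week of radiotherapy". This section cites Fig. 3 for the schedule, and that figure is not shown.

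The only other drug dosed per m² under Treatments is given as one figure: "Oxaliplatin 130 mg/m^2^, intravenously, on day 1".

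**The concern.** The drug, the figures 40–60 and the twice-daily frequency are the same in both places, but the unit is not. In the Chemotherapy section, 40–60 mg is the span of doses that the three BSA bands produce. In the Chemoradiation section the same span carries a per-m² unit, which would scale it by BSA again, and the article gives no reason for a different dose with radiation.

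This is the stated dose of the concurrent drug in the experimental arm, so it is part of the treatment contrast under test. Treatment toxicity is a secondary endpoint, and the Discussion names toxicity as an obstacle to completing preoperative therapy. Followed literally, the printed unit would put S-1 during radiation at or above the full SOX dose. A multicentre trial's published regimen should not leave that open.

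**Working it through.** **Inputs**

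- SOX bands (Chemotherapy section): 80 mg/day below 1.25 m²; 100 mg/day from 1.25 to below 1.5 m²; 120 mg/day from 1.5 m².
- Concurrent S-1 as printed (Chemoradiation section): 40–60 mg/m², twice daily.
- Patient BSA: an assumption, 1.0–2.0 m². The article reports no BSA values.

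**Step 1: reproduce the article's own SOX range.** Dose per administration = daily band dose / 2. This gives 80/2 = 40, 100/2 = 50 and 120/2 = 60 mg. The flat 40–60 mg range is therefore exactly the set of band doses, and the figures in that section are amounts per dose, not per day.

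**Step 2: put the SOX bands on a per-m² scale.** Daily dose per m² = band dose / BSA. It peaks at the lower edge of each band: 80/1.0 = 100/1.25 = 120/1.5 = 80 mg/m²/day. Within the assumed range it is lowest at 2.0 m²: 120/2.0 = 60 mg/m²/day. The bands therefore span 60–80 mg/m²/day.

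**Step 3: take the chemoradiation text literally, per dose.** 2 × 40 = 80 and 2 × 60 = 120, so 80–120 mg/m²/day.

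**Step 4: compare in mg/day.** Literal dose = 2 × (40 to 60) × BSA.

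| Assumed BSA (m²) | SOX band (mg/day) | Literal chemoradiation dose (mg/day) | Ratio to SOX band |
|---|---|---|---|
| 1.0 | 80 | 80–120 | 1.00–1.50 |
| 1.2 | 80 | 96–144 | 1.20–1.80 |
| 1.25 | 100 | 100–150 | 1.00–1.50 |
| 1.5 | 120 | 120–180 | 1.00–1.50 |
| 1.7 | 120 | 136–204 | 1.13–1.70 |
| 2.0 | 120 | 160–240 | 1.33–2.00 |

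The lower end of the printed range equals the SOX dose at 1.0, 1.25 and 1.5 m² and otherwise exceeds it, by up to 33%. The upper end is 1.5 to 2.0 times the SOX dose.

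**Step 5: remove the per-m² unit.** The chemoradiation dose becomes 40–60 mg twice daily, or 80–120 mg/day. This coincides with the three SOX bands, and the discrepancy disappears.

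**Step 6: ask whether the schedule could offset a higher daily dose.** S-1 is taken on 5 of 7 days during radiotherapy (71%) and on 14 of 21 days in SOX (67%). At 1.7 m² the literal dose averages 136 × 5/7 = 97 to 204 × 5/7 = 146 mg per calendar day, against 120 × 14/21 = 80 mg for SOX. The radiotherapy schedule does not bring the literal dose back to the SOX level.

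**The case against.** The strongest reply is that the two sections describe different regimens, so a different dose with radiation could be deliberate, and different doses would then not contradict each other. This cannot be excluded without Fig. 3 and the full protocol, which is why the misprint is called probable and no more. Against it stand the identical figures and frequency, the exact match with the bands once the unit is removed, and the lack of any stated reason for a higher dose with radiation.

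A second reply is that a journal article is not the dosing instruction used at sites and may leave detail to the full protocol. That is right for omissions. A reader might infer that the printed dose cannot be applied because no rule selects a value within 40–60 mg/m² and no daily maximum is given. The article does not support that as a finding: such rules are detail that it may leave out, and its SOX section already says "The dose of S-1 was accorded to body-surface area (BSA"), which offers an obvious selector if mg was meant. What the reply does not excuse is a stated unit that conflicts with the article's own text.

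A reader might also take 40–60 mg/m² as a daily total split over two doses, which would put it mostly below the SOX dose and make the text ambiguous by a factor of two. That rests on a comma. The SOX section uses the same construction, and its bands show that it means per dose.

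Finally, the size calculated above is conditional. If the unit is a slip, the true discrepancy is zero.

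**Conclusion.** The point holds as an internal unit inconsistency in the experimental-arm dose. The SOX section gives S-1 in mg by BSA band; the Chemoradiation section gives the same figures per m². A misprint is the likeliest explanation but is not proven.

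Taken literally and per dose, S-1 during radiation would range from about the full SOX dose to 1.5–2.0 times it. This assumes a BSA of 1.0–2.0 m² and that the printed range is per administration.

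Two wider conclusions are not supported. The article contains no dosing records, so it does not show that any patient received a wrong dose. The S-1 dose also does not enter the sample size calculation or the statistical analysis section, so the type I error, the power, the 682 patients and the planned tests are untouched. The correction is small, but worth making because it concerns a treatment dose.

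**What to change.** Check the full protocol and Fig. 3 first. If mg was meant, reword the Chemoradiation section along these lines: S-1 40–60 mg by mouth twice a day according to BSA (80, 100 or 120 mg per day in total, as for SOX), on days 1–5 of every radiotherapy week. If a per-m² dose was really meant, state the single mg/m² figure. If Fig. 3 carries the same unit, correct it as well.

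The cost is a one-line correction. No change to the design, sample size or analysis follows from it.

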**Fig. 3 Fig3:**
[figure not shown]
Chemoradiation schedule

#### Surgery

A standard D2 gastrectomy is recommended. The type of gastrectomy performed depends on the location and extent of the primary lesion. For middle third tumors, the gastric margin is recommended to be more than five cm, and a total gastrectomy is performed. For lower third tumors, a two cm duodenal margin is recommended and a subtotal or total gastrectomy is considered. For upper third tumors, a three cm esophageal margin is recommended and a total gastrectomy or esophagogastrectomy is performed. Billroth I or Roux-en-Y gastrojejunostomy is performed for distal gastrectomy patients, Roux-en-Y esophagojejunostomy is performed for patients receiving total gastrectomy.

#### Tumor response and toxicity criteria

In the preoperative chemoradiation arm, tumor response evaluations are taken after chemoradiation and second circle of preoperative SOX by using abdominal CT scan. In the preoperative chemotherapy arm, abdominal CT scan was performed to evaluate tumor response after third cycle of preoperative SOX. All these evaluations are done according to the Response Evaluation Criteria for Solid Tumors (RECIST) 1.1. Adverse events were assessed according to Common Terminology Criteria for Adverse Event (CTCAE) v4.0.

#### Follow up

Follow-up of all patients was carried out according to our protocol (every three months for at least two years, every six months for years 3–5, then every 12 months for life). Physical examination, tumor marker examination, and chest radiography were given every 3 months. Ultrasound and CT scan were given alternately every 6 months, and CT scan should be given at first follow-up. Endoscopic examination was given every 1 year [12].

### Sample size calculation

In this study, patients with cT3N + M0, cT4aN + M0 or cT4bN−/+M0 are recruited. According to AJCC 7th edition, these patients belong to stage IIB, IIIA, IIIB, and IIIC. We found that the 3-year disease free survival (DFS) of same stage patients after D2 gastrectomy and adjuvant chemotherapy is 41% in our database. Based on CLASSIC study, which showed that patient with II or III could get a 14% increase of 3-year DFS in adjuvant chemotherapy arm comparing to alone surgery arm [13], we speculate that 3-year DFS will be 27% for such stage patients after receiving alone D2 gastrectomy. Based on MAGIC study, which showed that patient could get a 13% increase of 3-year DFS in perioperative chemotherapy arm comparing to alone surgery arm [3], we speculate that 3-year DFS will be 40% for such stage patients after receiving perioperative chemotherapy. This study assumes a 10% increase in 3-year DFS favoring preoperative chemoradiation arm. Accrual time is four years followed by three years’ follow up. Dropouts are set 10%. It shows that a sample size of 682 will be needed with a 5% type I error (both sides) for a statistical power of 80%.

### Statistical analysis

DFS is calculated from the date of randomization to the date of detected disease recurrence. Following events are defined as recurrence: primary cancer recurrence, newly diagnosed gastric cancer, and death. OS is calculated from the date of randomization to the date of death or date of last follow-up. Survival is estimated by using the Kaplan-Meier method, and differences between survival curves are examined with log-rank test. Fisher’s exact is used to compare patients’ characteristics between preoperative chemotherapy arm and preoperative chemoradiation arm. Other secondary endpoints, including curative gastrectomy rate, pathological response rate, toxic effects, and postoperative complications, are compared between two arms using chi-square test. All statistical tests are two sides. The level of significance was *P* < 0.05.

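### DFS runs from randomization, but its event list omits failure to reach curative surgery, so such patients count as disease-free until death

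*Protocol article*

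**What the plan says.** The protocol article (Statistical analysis) fixes the origin and end of the primary endpoint: "DFS is calculated from the date of randomization to the date of detected disease recurrence". It then lists what counts: "Following events are defined as recurrence: primary cancer recurrence, newly diagnosed gastric cancer, and death".

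Other sections show that the omitted failures are possible and would be seen:

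- Inclusion criteria: tumour is in place at entry, and patients need only be "Considered to be potentially resectable verified by a multi-disciplinary team including a surgical investigator".
- Background: in the group's own previous study, "67% patients with locally advanced gastric cancer received curative gastrectomy after receiving chemoradiation".
- Secondary endpoint: reaching curative surgery is a separate outcome, in the list "3-year overall survival (OS), curative gastrectomy rate, pathological response rate".
- Tumor response and toxicity criteria: both arms have CT before surgery, and "All these evaluations are done according to the Response Evaluation Criteria for Solid Tumors (RECIST) 1.1".

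None of these sections links preoperative progression or a failed resection to DFS.

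**The concern.** An event list built on recurrence suits patients whose tumour has been removed. Here the clock starts while every patient still has disease. Three groups never become disease-free: those who progress or metastasise during preoperative treatment, those found unresectable or metastatic at operation, and those with a macroscopically incomplete resection. Under the stated list their only event is death, or they are censored alive.

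Getting patients to curative surgery is a main early route by which preoperative chemoradiation and preoperative chemotherapy could differ. If they do differ there, in either direction, the primary endpoint registers it only through later deaths. The reported DFS curve would also include patients who were never free of disease.

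**Working it through.** **The plan's own figure.** The planned 3-year DFS is 40% against 50% (Sample size calculation).

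- HR = ln 0.50 / ln 0.40 = 0.756.
- Schoenfeld events, two-sided 5%, 80% power, 1:1 allocation (assumed): 4 × (1.960 + 0.842)² / (ln 0.756)² ≈ 404.
- With 4 years of uniform accrual, 3 further years, exponential survival and 10% dropout per year, the event probability is 0.593, so N = 404 / 0.593 ≈ 681.

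The stated 682 is reproduced, so the sample size is not in dispute.

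**How many never-disease-free patients sit in the curve.** Assume failure at month 4 and exponential survival afterwards with a 12-month median. A failing share q adds q × 0.5^((t − 4)/12) to apparent DFS at month t.

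| q | added at 12 months | added at 36 months |
|---|---|---|
| 33% | 20.8 points | 5.2 points |
| 20% | 12.6 points | 3.1 points |
| 10% | 6.3 points | 1.6 points |

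If 55% of resected control patients are disease-free at 3 years (assumed) and 33% fail, true DFS is 0.67 × 55% = 36.9% and the stated rule shows 36.9 + 5.2 = 42.1%. The early curve moves more than the 3-year value, and the planned log-rank test uses the whole curve.

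**Effect on the test.** The simulation used 682 patients, 3 to 7 years of follow-up, no dropout, exponential DFS in resected patients (55% at 3 years in control), failure at about month 4 (spread about half a month) in both arms, and a log-rank test. With 2,000 simulated trials the standard error of a power is about 1 point, and repeat runs agreed to within 1 to 2 points. Failure shares, survival after failure and hazard ratios in resected patients are assumptions.

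| Failures, Pre-CT vs Pre-CRT | HR in resected | Median survival after failure | Power, stated list | Power, failures counted |
|---|---|---|---|---|
| 33% vs 23% | 0.85 | 12 months | 65% | 81% |
| 33% vs 23% | 0.85 | 18 months | 51% | 80% |
| 33% vs 23% | 1.00 | 12 months | 18% | 39% |
| 20% vs 13% | 0.80 | 12 months | 75% | 83% |
| 15% vs 10% | 0.80 | 12 months | 70% | 77% |
| 10% vs 7% | 0.76 | 12 months | 82% | 83% |
| 20% vs 20% | 0.76 | 12 months | 59% | 54% |
| 33% vs 33% | 0.76 | 12 months | 45% | 38% |

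If Pre-CRT had more failures (33% vs 23%) and an HR of 0.80 in resected patients, the stated list gives an overall HR of about 0.96, against about 1.02 when failures count.

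**Dating the failures.** Pre-CT has 3 × 3 = 9 weeks of preoperative treatment. Pre-CRT has 2 × 3 weeks of SOX, a one-week gap and 5 weeks of radiation, about 12 weeks. If failures were dated when first documented, Pre-CRT failures would fall about 3 weeks later with no real benefit. Under a true null with 33% failing in each arm, that offset gives a type I error of about 12%, against 5 to 6% under the stated list. With 20% failing it is about 6%, and with 33% failing and a 5-week offset about 18%. One common date in both arms brings it back to about 5%.

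**The case against.** The strongest reply concerns size. A reader might infer from the 67% that about a third of PREACT patients would be misclassified. The documents do not support that. The figure comes from a previous study whose population is not shown. PREACT requires a multidisciplinary judgement of resectability, and staging laparoscopy or laparotomy (Recruitment) with peritoneal cytology (Discussion), which should remove some of these cases. Lack of curative gastrectomy may also reflect microscopic residual disease, refusal or toxicity, which is wider than the group at issue. This objection stands.

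A reader might also infer that the stated endpoint is invalid or produces false positives. It does not. Deaths are events, so these patients are counted, only late, and with equal failures and no treatment effect the type I error stays near 5%. The loss of power needs a gap between the arms. Without one, the stated list has slightly more power.

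Finally, the article is condensed and does not define recurrence of the primary cancer, so the full protocol might treat preoperative progression as recurrence. That does not remove the point. The article gives a complete list for its primary endpoint, and that list does not fit its time origin. If sites supplied their own reading, the endpoint would be applied inconsistently between two visibly different treatments.

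**Conclusion.** The point holds as a flaw in the stated primary-endpoint rule; it is more than a detail left to a fuller document. From randomization, the listed events cannot register failure to become disease-free except through death. The consequence is a delayed or hidden contrast whenever the arms differ in reaching curative surgery, and a DFS curve that includes patients never free of disease.

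The size cannot be fixed from the document. Under the assumptions above, the power lost runs from about 16 points (33% vs 23% failing) through about 8 (20% vs 13%) to about 1 (10% vs 7%). With equal failure rates nothing is lost. With 12-month survival after failure, the 3-year estimate is raised by about 2 to 5 points for 10% to 33% failing.

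**What to change.** Amend the DFS definition in Statistical analysis so that these also count as primary-endpoint events:

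- progression or metastasis before surgery;
- unresectable or metastatic disease found at operation;
- macroscopically incomplete resection.

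Date all of them at one common time from randomization in both arms, late enough to cover planned surgery in the longer Pre-CRT schedule. Deaths before that time keep their own date. The text shown gives no interval to surgery, so the sponsor has to set the date from the full schedule. Keep the present definition as a sensitivity analysis.

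No new data should be needed: preoperative CT is planned in both arms and curative gastrectomy is already an endpoint. There are three costs.

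- Stated 3-year DFS will be lower in both arms.
- The planning rates need re-justifying, and with them the 682. They start from 41% in patients after D2 gastrectomy, who had all reached surgery (41 − 14 = 27%; 27 + 13 = 40%; 40 + 10 = 50%).
- The powers above place failures at about month 4. A check with all failures tied at one later date kept type I error near 5% but returned somewhat less of the gain, so power should be recomputed for the date chosen.

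### Randomisation is stratified by Lauren classification, but the log-rank test named for DFS and OS carries no strata; stratifying it costs nothing and recovers a little power if Lauren type is prognostic

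*Protocol article*

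**What the plan says.** The Study setting section of the protocol article describes the allocation: "Patients were randomized by the way of stratified permutated block randomization on Web-based system. Lauren classification is stratification factor". No other stratification factor is named.

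The Statistical analysis section gives Kaplan-Meier estimation for survival and then the test: "differences between survival curves are examined with log-rank test". It does not mention Lauren classification, and it does not call the test either stratified or unstratified. The Sample size calculation section does not mention Lauren type either. It sets the control rate ("we speculate that 3-year DFS will be 40% for such stage patients after receiving perioperative chemotherapy") and the effect ("This study assumes a 10% increase in 3-year DFS favoring preoperative chemoradiation arm"), with 5% two-sided type I error, 80% power and 682 patients. The article gives neither the expected Lauren mix nor any prognostic effect of Lauren type.

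**The concern.** Blocking within Lauren strata forces the arms to be nearly balanced on Lauren type. If Lauren type affects DFS, this removes one source of chance difference between the arms. A log-rank test that pools all patients in one risk set still counts that source in its variance. It therefore rejects too seldom under the null and has less power under the alternative than a test that compares the arms within strata and sums over strata.

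What is at stake is efficiency, and agreement between design and analysis. There is also a pre-specification interest. If only an unqualified log-rank is on record, a later choice between the plain and the stratified result could be challenged.

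**Working it through.** **Step 1. Reproduce the planned sample size.** The inputs from the Sample size calculation section are 40% against 50% at 3 years, 5% two-sided, 80% power, 4 years of accrual plus 3 of follow-up, and 10% dropout. Assumptions: 1:1 allocation, exponential DFS, uniform accrual, and dropout of 10% per year (the article does not say whether it is per year or in total).

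- Hazards per year: control −ln(0.4)/3 = 0.3054; chemoradiation −ln(0.5)/3 = 0.2310; hazard ratio ln(0.5)/ln(0.4) = 0.756.
- Events (Schoenfeld): 4 × (1.960 + 0.842)² / (ln 0.756)² = 31.40 / 0.0779, about 403.1, rounded up to 404.
- Dropout hazard: −ln(0.9) = 0.105. With h = λ + 0.105, the probability of an observed event is (λ/h) × [1 − (e^(−3h) − e^(−7h)) / (4h)]. This gives 0.637 for control and 0.549 for chemoradiation, mean 0.593.
- Patients: 404 / 0.593 = 681.1, rounded up to 682, as stated.

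The formula that reproduces 682 is for an unstratified log-rank. It would serve equally as the starting point for a trial analysed with strata, so it does not show which test is intended.

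**Step 2. Compare the two tests under the design.** Simulation with 682 patients, permuted blocks of 4 within Lauren strata, accrual, follow-up and dropout as in Step 1, and 10,000 trials per cell. In each scenario the baseline hazard was set so that overall control DFS at 3 years is 40%. The within-stratum treatment hazard ratio was set so that overall chemoradiation DFS is 50%. Lauren mix, Lauren hazard ratios and block size are assumptions.

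| Assumed Lauren strata (hazard ratio) | Within-stratum treatment HR | Type I error, plain | Type I error, stratified | Power, plain | Power, stratified | Power difference (points) |
|---|---|---|---|---|---|---|
| Two equal (1.0) | 0.757 | 0.050 | 0.050 | 80.4% | 80.3% | −0.1 |
| Two equal (1.25) | 0.755 | 0.048 | 0.048 | 79.6% | 79.9% | 0.3 |
| Two equal (1.5) | 0.753 | 0.047 | 0.052 | 80.2% | 81.2% | 1.0 |
| Two equal (2.0) | 0.746 | 0.042 | 0.052 | 79.5% | 82.5% | 3.0 |
| 40/40/20% (1 / 1.5 / 1.25) | 0.754 | 0.046 | 0.048 | 80.9% | 81.7% | 0.8 |

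Simulation error is about 0.2 points for type I error and 0.4 points for power. The 0.3 points at a hazard ratio of 1.25 is therefore within noise, and the stratified test's 0.052 is compatible with 5%.

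**Step 3. Check the other reading of dropout.** Here dropout is 10% in total and the within-stratum treatment hazard ratio is held at 0.756. Power is higher, but the pattern is the same: 84.9% plain against 85.8% stratified at a Lauren hazard ratio of 1.5, and 82.4% against 85.9% at 2 (type I error 0.041 against 0.051). At a hazard ratio of 3 the figures are 75.1% against 84.6%, with type I error 0.030. Nothing in the article supports a Lauren effect that large. With the within-stratum effect held fixed, the overall 3-year difference is then also smaller than the planned 10 points. That case shows only that the loss grows with the prognostic effect.

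**Step 4. Put the gain in terms of events.** From the power z-values at a Lauren hazard ratio of 2: (1.960 + 0.935)² / (1.960 + 0.824)² = 8.381 / 7.751 = 1.081. That is roughly 8% more information, or about 33 of the 404 events. At 1.5 it is (1.960 + 0.884)² / (1.960 + 0.847)² = 8.088 / 7.879 = 1.027, or roughly 10 events. This is a rough conversion, because part of the gain comes from restoring the nominal significance level.

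**The case against.** The strongest objection is that the article does not say the test is unstratified. A stratified log-rank is still a log-rank test, the article condenses a full protocol, and whether the test uses the randomisation strata is a detail often left to the SAP. This stands to the extent that nobody can conclude from the article that the trial will be analysed without strata. It does not remove the point. The article names the test for the survival endpoints, and a better-matched version of that test is available at no cost.

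The second objection is that any loss depends on Lauren type being prognostic, and the article gives no figure for this. That stands in full. The choice of Lauren type as the only named stratification factor suggests that the investigators expect it to matter, but that is an inference.

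A reader might also infer more than the article supports:

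- *That the primary test is invalid or the trial underpowered.* It is not. The error of ignoring strata is on the conservative side, and the plain test keeps 79.5% to 80.9% power in every scenario run at the planned 40% against 50%.
- *That leaving out clinical stage is part of the same error.* Stage is not a stratification factor, so the argument for analysing as randomised does not reach it. Any gain from adjusting for it would rest on assumed stage effects.
- *That the binary secondary endpoints, which "are compared between two arms using chi-square test", need Cochran-Mantel-Haenszel tests.* The same logic could be applied, but no loss has been shown for them.
- *That a hazard ratio nearer 1 is a defect.* The design is powered on overall 3-year DFS rates. Overall and within-stratum hazard ratios are different quantities, and neither is wrong.

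**Conclusion.** The point holds as a minor efficiency and consistency improvement. Randomisation uses Lauren strata and the stated survival test mentions none. If Lauren type is prognostic and the test is run without strata, the plan forgoes about 0.3, 1 or 3 points of power at assumed between-stratum hazard ratios of 1.25, 1.5 or 2, and at 2 tests at about 4% instead of 5%. If Lauren type is not prognostic, the two tests perform alike (80.4% against 80.3%).

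The stated sample size reproduces, and over this range neither the planned power nor the 5% limit is undermined. The figures rest on assumed Lauren mix and effects, 1:1 allocation, exponential DFS and 10% annual dropout.

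**What to change.** In the Statistical analysis section, state that the primary comparison of DFS, and the comparison of OS, use a two-sided log-rank test stratified by Lauren classification as recorded at randomisation, with the unstratified log-rank as a sensitivity analysis. If the full protocol or SAP already specifies this, only the article's wording needs to be aligned. If an unstratified primary test is intended, give the reason.

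The cost is one sentence. It needs no new data, no extra patients and no change to the 682. The choice should be fixed before outcome data are compared by arm. Adjustment for clinical stage and stratified tests for the binary endpoints are optional and not part of this request.
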